## Abstract

The worldwide prevalence of overweight and obesity in women of reproductive age is rapidly increasing and a risk factor for the development of gestational diabetes (GDM). Excess adipose tissue reduces insulin sensitivity and may underlie adverse outcomes in both mother and child. The present paper describes the rationale and design of the PRegnancy Outcomes and Maternal Insulin Sensitivity (PROMIS) study, an exploratory cohort study to obtain detailed insights in insulin sensitivity and glucose metabolism during pregnancy and its relation to pregnancy outcomes including early infancy growth. We aim to recruit healthy pregnant women with a body mass index (BMI) ≥ 25 kg/m^2^ before 12 weeks of gestation in Northern Netherlands. A total of 130 woman will be checked on fasted (≤7.0 mmol/L) or random (≤11.0 mmol/L) blood glucose to exclude pregestational diabetes at inclusion. Subjects will be followed up to six months after giving birth, with a total of nine contact moments for data collection. Maternal data include postprandial measures following an oral meal tolerance test (MTT), conducted before 16 weeks and repeated around 24 weeks of gestation, followed by a standard oral glucose tolerance test before 28 weeks of gestation. The MTT is again performed around three months postpartum. Blood analysis is done for baseline and postprandial glucose and insulin, baseline lipid profile and several biomarkers of placental function. In addition, specific body circumferences, skinfold measures, and questionnaires about food intake, eating behavior, physical activity, meal test preference, mental health, and pregnancy complications will be obtained. Fetal data include assessment of growth, examined by sonography at week 28 and 32 of gestation. Neonatal and infant data consist of specific body circumferences, skinfolds, and body composition measurements, as well as questionnaires about eating behavior and complications up to 6 months after birth. The design of the PROMIS study will allow for detailed insights in the metabolic changes in the mother and their possible association with fetal and postnatal infant growth and body composition. We anticipate that the data from this cohort women with an elevated risk for the development of GDM may provide new insights to detect metabolic deviations already in early pregnancy. These data could inspire the development of new interventions that may improve the management of maternal, as well as offsrping complications from already early on in pregnancy with the aim to prevent adverse outcomes for mother and child.

## 1. Introduction

Insulin sensitivity normally decreases by the end of the second trimester due to the effect of placental hormones, such as human placental lactogen (HPL), progesterone, and human placental growth hormone, to ensure a continuous supply of nutrients to the growing fetus [1,2]. Decreased insulin sensitivity leads to beta-cell proliferation and a larger volume of individual beta-cells, returning to non-pregnant levels after parturition. Hyperglycemia may develop due to insufficient beta-cell proliferation [3,4,5,6]. However, the mechanism behind insulin resistance is multifactorial. Women with a body mass index (BMI) ≥ 25 kg/m^2^ have excess adipose tissue which is known to reduce insulin sensitivity and may explain the correlation with adverse outcomes of pregnancy for both mother and child [7]. The worldwide prevalence of overweight and obesity during pregnancy is rapidly increasing, with a prevalence of nearly 54 million worldwide [8]. In the Netherlands, the prevalence of overweight women age 30–40 years was 39% in 2017 and around 44% in 2019 [9], suggesting that many women are already overweight when becoming pregnant. The physiological insulin resistance during pregnancy in combination with overweight or obesity could increase the risk for hyperglycemia. The hyperglycemia and pregnancy outcomes (HAPO) study has shown that already small increases in maternal glucose levels show a linear relationship with adverse outcomes [10].

Insulin resistance during pregnancy increases the risk of pregnancy complications such as pregnancy induced hypertension, pre-eclampsia, caesarian section and gestational diabetes mellitus (GDM), and excessive pregnancy weight gain during pregnancy and weight retention postpartum, while longer term it also increases the risk of cardiovascular diseases and diabetes mellitus (DM) type 2 and other non-communicable diseases. Adverse outcomes of pregnancy hyperglycemia in infants could be macrosomia and large for gestational age (LGA), as well as neonatal complications on the short term and a higher risk on childhood obesity and non-communicable diseases longer term [7].

Maintaining euglycemia despite the developing insulin resistance over the course of pregnancy is critical. Deviations in maternal glucose metabolism could potentially already be detected early in pregnancy [7,10,11]. Yet, potential hyperglycemia is currently standardly examined at the end of the second trimester by an oral glucose tolerance test (OGTT), and in the Netherlands only in an at-risk population defined as BMI ≥ 30 kg/m^2^ [12]. This test, taking baseline and 2-h blood glucose levels as a result, is not suitable to detect mild hyperglycemia in early pregnancy and shows considerable within subject variability [13]. Markers of insulin sensitivity and related metabolic adaptations, for instance in lipid metabolism, may be a more straightforward measure in which deviations could potentially be detected earlier [14]. An integration of postprandial responses of glucose and insulin combined with lipid markers following a challenge test would provide clearer insights in maternal metabolic function. To this end, a meal tolerance test (MTT), which contains a well-defined balanced macro- and micronutrient composition may be much more sensitive than the standard OGTT. Assessing glucose homeostasis based on glucose concentrations only is not reliable as there are numerous perturbations where glucose production and its utilization increases or decreases to the same extent without any changes in blood concentrations [15]. For the understanding of the physiology and pathophysiology of glucose uptake and metabolism during pregnancy, glucose tracers could be used [16].

The design of the Pregnancy Outcomes and Maternal Insulin Sensitivity (PROMIS) study will allow collection of detailed insights in insulin sensitivity and glucose metabolism during (early) pregnancy in women with overweight and obesity and assess its possible relation to growth and body composition during of the offspring during the fetal and early infancy period. We hypothesize that using an MTT, disturbed insulin sensitivity in overweight pregnant women could be identified much earlier in pregnancy. Early detection could help to better predict the risk of possible adverse outcomes short term and reduce the risk of non-communicable diseases on the longer term.

## 2. Materials and Methods

### 2.1. Overall Study Design

The PROMIS study is a multi-center exploratory prospective cohort-based study in the two Northern provinces of the Netherlands (Groningen and Friesland). The study has been approved by the medical ethical committee University Medical Centre Groningen prior to the start of the study (NL68845.042.19) and is registered at ClinicalTrials.gov (NCT04315545). Healthy pregnant women with a BMI ≥ 25 kg/m^2^ are eligible for participation. Weight and height of women as well as fasting glucose levels will be confirmed via measurements by study staff at inclusion. Study duration will be from 12 weeks of gestation up to 6 months after giving birth with a total of nine contact moments when data will be collected. The MTT will be performed between weeks 12 and 16 and repeated between weeks 24 and 28 of gestation and three months postpartum. A standard OGTT will be performed after the second MTT, also between weeks 24 and 28 of gestation. In addition, maternal anthropometrics will be assessed at the time of the MTT challenges. Additional sonographies will be made during gestation at week 28 and 32 to assess fetal growth. Neonatal and infant anthropometrics will be obtained after birth and at 1, 2, 3, 4, and 6 months of age from the records of the baby clinic visits. Body composition measurements using an air displacement plethysmography (Pea Pod, COSMED, Rome, Italy) [17] will be performed at 1, 3, and 6 months of age. Questionnaires about nutrition and lifestyle will also be collected at several time points throughout the study. A study overview is depicted in Figure 1.

### 2.2. In-and Exclusion Criteria

Inclusion criteria are singleton pregnancy, BMI ≥ 25 kg/m^2^, fasted (≤7.0 mmol/L) or random (≤11.0 mmol/L) blood glucose level, aged ≥ 18 years, and written informed consent. Women will be excluded from the study if they have pre-existing DM type 1 or 2, serious health complications (hypertension, hyperlipidemia, asthma, haemochromatosis) or medication use that influences the glucose metabolism or fetal growth (e.g., chronic use of corticosteroids). In addition, women who are participating in any other studies involving investigation of medication or nutritional products, have a severe illness, psychological dysfunctions, used antibiotics two weeks prior to participation, have HIV or hepatitis, expected to not comply to the study protocol (e.g., fear of needles), known allergies or intolerances for one or more nutritional ingredient used in the MTT will also be excluded.

### 2.3. Recruitment

Women will be recruited in the provinces of Groningen and Friesland from a diverse range of socio-economic and ethnic backgrounds. Hospitals, midwife practices, ultrasound practices, and family doctor’s practices are involved in recruitment. To optimize recruitment, flyers were made, and social media accounts set up. Information sheets explaining aspects of the study, as well as a short video explaining the study set up will be provided to eligible participants. Women will have the opportunity to consider participation and to ask questions to the researchers and can terminate participation at any time within the study without affecting their usual care. The privacy of the participant will be ensured via protected data collection and processing by the researchers and will be saved anonymously. Written informed consent will be obtained prior to the first baseline measurement. Women are requested to give consent for (1) participation in the study, including taking of blood samples, collecting associated measurements, and extraction of relevant data from medical records; (2) storage of blood in a bio bank and (3) participation of their child in this study including gathering protocol specified measurements.

### 2.4. Meal Tolerance and Oral Glucose Tolerance Testing

To conduct the MTT, a non-investigational product, Nutridrink Compact, will be used. Nutridrink Compact is a liquid product for medical use to treat malnutrition. It provides energy and nutrients in a relatively compact volume and contains a suitable combination and levels of macro- and micronutrients, largely comparable to the energy and nutrient composition of a standard breakfast. The product volume will be standardized to 50 gr carbohydrates and contains 24 g of protein and 9 g of fat, equivalent to 404 kcal in a total volume of 169 mL. The study participants are asked not to eat or drink (except for water) anything from 11 pm before the test day to arrive in the fasted state. For regular OGTT testing, a standard 75 gr glucose solution of 200 mL will be used. Participants will be diagnosed with GDM when plasma blood glucose is ≥7.0 mmol/L in fasted state or ≥7.8 mmol/L 2 h after the OGTT. These guidelines are according to the Dutch Association of Obstetrics and Gynecology (NVOG) [18]. In a subgroup of participants (estimate *n* = 20) we will add 2% of the total amount of carbohydrates in the MTT as glucose tracers. In total, 1.25 g of D-(6,6-D2, 99%)-glucose, used as the tracer, will be added to the MTT, as well as to the OGTT, selected to ensure participant and experimental safety [19]. The solution will be prepared by the research pharmacy in special units that require only the addition of the required MTT or OGTT volume. In both the MTT and the OGTT, the participant should ingest the drink within 5 min.

### 2.5. Sample Size Calculation

The primary outcome of the PROMIS study is to detect changes in blood glucose- and insulin levels following an MTT, containing 50 g of carbohydrates next to other nutrients. The null hypothesis is that early pregnancy assessment of maternal glucose-insulin metabolism with an MTT will identify more mothers at risk for pregnancy complications compared to a standard OGTT conducted at the end of the second trimester. The current prevalence of GDM, a state of reduced insulin sensitivity leading to hyperglycemia based on standard OGTT testing, is estimated to be 3–5% in the Netherlands, as diagnosed between 24–28 weeks of gestation. Given the reported linear relationship between blood glucose and adverse outcomes [10] and higher rates of insulin resistance with increased BMI [20], more heterogeneity, disturbances in blood glucose, and insulin values are expected in our study population than the indicated 3–5% [21] for the total population of pregnant women in the Netherlands. In addition, we anticipate that the first abnormal blood values, in particular signs of insulin resistance might already be detected in early gestation using this more physiological testing paradigm. To be able to reject the null hypothesis, we estimate that a total of 130 pregnant women are needed to participate in the PROMIS study, allowing for a dropout rate of 20%. This is based on an expected sensitivity of 74% and a minimal lower confidence limit of 0.62 in OGTT’s containing 50 g of carbohydrates, given before 32 weeks of gestation for observational studies [22,23]. Given the exploratory nature of the study, the sample size will be re-estimated after the first OGTT has been completed in 25 subjects based on available sensitivity and specificity data.

### 2.6. Interim Analysis

After including a total of 5 participants that completed the first MTT, a first interim analysis will be performed to see if the added amount of glucose tracer is indeed sufficient to trace glucose fate following the MTT. If the amount of glucose tracer is insufficient for analysis, the size of the subgroup and the percentage of added glucose tracer can be adjusted. The first interim will also be used to assess possible unexpected adverse events. A second interim analysis will be done after the completion of the OGTT in the first 25 subjects to recalculate the sample size by sensitivity and specificity after confirmation of GDM incidence based on blood glucose levels. It is expected that the final number for inclusion will be lower than the calculated 130 participants given the detailed data collection to assess glucose-insulin metabolism.

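### Re-estimating the sample size from sensitivity and specificity after 25 OGTTs rests on too few GDM cases, and the expected fall below 130 has no support in the plan's own inputs

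*Protocol article*

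**What the plan says.** Section 2.5 (Sample Size Calculation) bases the total of 130 women, including 20% dropout, on "an expected sensitivity of 74% and a minimal lower confidence limit of 0.62". It then states that "the sample size will be re-estimated after the first OGTT has been completed in 25 subjects based on available sensitivity and specificity data". Section 2.6 (Interim Analysis) repeats this: the second interim comes "after the completion of the OGTT in the first 25 subjects to recalculate the sample size by sensitivity and specificity", once GDM incidence has been confirmed from glucose values. The same section adds: "It is expected that the final number for inclusion will be lower than the calculated 130 participants". The reason given there is the detail of the glucose and insulin data.

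A case is defined in Section 2.4: "Participants will be diagnosed with GDM when plasma blood glucose is ≥7.0 mmol/L in fasted state or ≥7.8 mmol/L 2 h after the OGTT". The only GDM prevalence in the article is in Section 2.5, "estimated to be 3–5% in the Netherlands, as diagnosed between 24–28 weeks of gestation". That figure is for all pregnant women. The section says that more disturbed values "are expected in our study population than the indicated 3–5% [21] for the total population of pregnant women in the Netherlands", but gives no figure for this cohort.

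Section 2.8 says that an analysis plan will be written for each interim analysis.

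**The concern.** The denominator of sensitivity is the number of women with the condition, not the number tested. With 25 women tested and an uncommon condition, that denominator is a handful at best and may be zero. A sample size recalculated from such an estimate mainly reflects whether one or two particular women happened to test positive.

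The sections also state in advance which way the number is expected to move. A noisy estimate read with the expectation of a smaller study could cut a cohort that is already short of cases for the precision it states. Section 3 already warns that the power estimate may not support many of the secondary outcomes, and fewer women would make that worse.

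**Working it through.** **Inputs from the document.** Interim size 25 (Sections 2.5, 2.6); sensitivity 0.74 and lower limit 0.62 (2.5); total 130 with 20% dropout, so 130 × 0.8 = 104 completers (2.5); prevalence 3–5% in the general pregnant population (2.5).

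**Assumptions.** The article gives no prevalence for women with BMI ≥ 25, so 10%, 20% and 30% are tried. GDM on the OGTT is taken as the target condition, because it is the only one Section 2.6 names at this interim. True sensitivity is taken as the planning value, 0.74.

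**Step 1: can 130 be reproduced?** Not from the stated inputs alone, because neither the power nor the cohort prevalence is given. The nearest standard match assumes 80% power and a two-sided 5% test of 0.74 against 0.62 with the variance at 0.74: (1.96 + 0.842)² × 0.74 × 0.26 / 0.12² = 104.9. Rounded up, 105 / 0.8 gives 132; rounded down, 104 / 0.8 = 130. This match was found after trying many variants, so the derivation remains undetermined. If it is the one used, the 104 counts GDM cases, not women.

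**Step 2: cases at the interim.** Expected cases = 25 × p. The chance of no case is (1 − p)^25.

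**Step 3: how often sensitivity is unusable.** The estimate is undefined with no cases, and is exactly 100% or 0% when all or none of the cases are detected. Summing over the binomial number of cases gives

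P = (1 − 0.26p)^25 + (1 − 0.74p)^25 − (1 − p)^25.

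For p = 0.05: 0.721 + 0.390 − 0.277 = 0.833.

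| Prevalence p | Expected cases in 25 | P(no case) | P(undefined, 0% or 100%) |
|---|---|---|---|
| 3% | 0.75 | 47% | 93% |
| 5% | 1.25 | 28% | 83% |
| 10% (assumed) | 2.5 | 7% | 59% |
| 20% (assumed) | 5 | 0.4% | 28% |
| 30% (assumed) | 7.5 | 0.01% | 13% |

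**Step 4: precision when an estimate exists.** Exact (Clopper-Pearson) 95% intervals are 0.025–1.00 for 1/1, 0.28–0.99 for 4/5 and 0.35–0.97 for 6/8. The whole planning margin is 0.74 − 0.62 = 0.12. With 5 cases one woman moves the estimate by 1/5 = 0.20, and with 8 cases by 1/8 = 0.125. A single result therefore moves the estimate by more than the margin that the sample size is built on.

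**Step 5: which way an informative recalculation would point.** Cases needed for a Wald 95% lower limit of 0.62 at an estimate of 0.74: 1.96² × 0.74 × 0.26 / 0.12² = 51.3, so 52 (63 by Wilson, 69 by Clopper-Pearson). Women to enrol = 52 / p / 0.8:

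- 3%: 2,167
- 5%: 1,300
- 10%: 650
- 20%: 325
- 30%: 217

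All exceed 130. For 104 completers to contain 52 cases, prevalence would have to be 52 / 104 = 50%.

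**The case against.** Several arguments on the other side have force.

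- **Prevalence.** The 3–5% is a general-population figure that Section 2.5 expects this cohort to exceed. A reader might infer that the interim will hold about one GDM case. The document does not support that as a prediction; it holds only at the quoted rate. The argument therefore has to survive higher rates, and it does up to 30%.
- **The interim is not only about accuracy.** Section 2.6 also confirms GDM incidence, which is a proper planning quantity. Specificity would rest on about 17 to 24 non-cases and is less affected. Both points stand, but the stated basis of 130 is sensitivity.
- **No stopping rule.** A reader might infer that the study could stop on a favourable accuracy estimate, biasing the final sensitivity upward. Neither section contains a stopping rule or success boundary, so that reading is not supported. Nor is the formula for recalculation given, so it cannot be said how often the number would shrink under it.
- **The reduction is an expectation, not a decision.** Section 2.6 attributes it to the detailed data, not to interim sensitivity. That is fair, but the reason does not work for sensitivity: more samples per woman do not add women with GDM.
- **An interim analysis plan is promised.** It may supply the rule, a floor or a minimum number of cases. It cannot change how many cases 25 women yield.
- **The study is exploratory.** Its primary outcomes are glucose and insulin responses (Section 2.5) and their AUC in relation to fetal growth and birth weight (Section 3), not diagnostic accuracy. This lowers the severity but does not make the recalculation informative.

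**Conclusion.** The concern holds in this form: a sample size recalculated from sensitivity after 25 OGTTs would be set largely by chance at every prevalence from 3% to 30%. The estimate is unusable in 93% to 83% of interims at the quoted 3–5%, and in 59% to 13% at an assumed 10–30%. Where it is usable, its interval is several times wider than the 0.12 planning margin. The expectation of fewer than 130 women has no support in the stated precision target, which calls for more than 130 throughout that range.

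The percentages assume a true sensitivity of 0.74 and GDM on the OGTT as the target condition. The 10–30% range is an assumption, not a figure from the article.

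Severity: should be fixed. The remaining risk is a smaller cohort chosen on noise, not a distortion of the primary glucose and insulin analyses.

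**What to change.** Reword Sections 2.5 and 2.6 as follows.

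1. Remove interim sensitivity and specificity as the basis for changing the sample size.
2. At the 25-woman interim, use the observed GDM proportion with its confidence interval, and the observed dropout, to restate the precision for sensitivity that 130 women will give. The interval matters: 5 cases in 25 gives an exact 95% interval of 7% to 41%. As an illustration, 104 completers at 20% prevalence would contain 104 × 0.20 = 20.8 cases, with a Wald half-width of 1.96 × √(0.74 × 0.26 / 20.8) = 0.19 and a lower limit near 0.55, not 0.62.
3. State that the number will not be revised downward on this basis.
4. Delete the sentence expecting a final number below 130.

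The cost is a rewording of two sections and the loss of the option to reduce the number at this interim. Planned recruitment stays at 130. This does not make 130 adequate for the stated precision; it makes the shortfall visible and keeps it from growing by chance.

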#### 2.7.5. Other Outcomes

Social demographics recorded include marital status, household composition, occupation, ethnicity, financial household income, level of education, and paternal information. The questionnaire used includes family history of DM, previous GDM diagnosis, birth weight of previous pregnancy (if any), more detailed questions about previous child or children born, polycystic ovary syndrome (PCOS), medication use, pregnancy eclampsia, and pre-pregnancy hypertension. In addition, obstetrical and perinatal complications during and after pregnancy will be registered, such as spontaneous or induced abortion, intrauterine death, preeclampsia, pre-term delivery (<37 weeks), need for labor induction, assisted vaginal delivery, shoulder dystocia, caesarian section. Finally, adverse events related to the neonate/infant such as macrosomia, large for gestational age, small for gestational age, hypoglycemia, respiratory distress, neonatal hospitalization, and other complications (if any) will be recorded.

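### The sample size and its re-estimation rest on sensitivity and specificity, apparently against OGTT-defined GDM, and so do not support the hypothesis that the early MTT finds more at-risk mothers than the OGTT

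*Protocol article*

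**What the plan says.** - **Hypothesis (section 2.5).** The early MTT "will identify more mothers at risk for pregnancy complications compared to a standard OGTT conducted at the end of the second trimester". This is labelled the null hypothesis, although it is plainly what the study hopes to show.
- **Sample size (section 2.5).** The article states that "a total of 130 pregnant women are needed to participate in the PROMIS study, allowing for a dropout rate of 20" per cent. The basis is an "expected sensitivity of 74% and a minimal lower confidence limit of 0.62", taken from literature on 50 g OGTTs.
- **Re-estimation (sections 2.5 and 2.6).** N will be revised "based on available sensitivity and specificity data". Section 2.6 places this "after the completion of the OGTT in the first 25 subjects" and says the aim is to "recalculate the sample size by sensitivity and specificity after confirmation of GDM incidence based on blood glucose levels". It expects the final number to fall below 130.
- **Definition of GDM (section 2.4).** Fasting glucose of at least 7.0 mmol/L, or at least 7.8 mmol/L two hours after the OGTT.
- **Outcomes available.** Section 2.7.5 says that "obstetrical and perinatal complications during and after pregnancy will be registered". The Discussion gives the primary outcome as the association of fasting and postprandial glucose and insulin with fetal growth and birth weight.

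**The concern.** The hypothesis compares two tests, and its target is risk of pregnancy complications. The quantities that set N describe one test, and the re-estimation appears to judge that test against a diagnosis made with the other. Under such a reference the OGTT is perfect by definition, and the MTT can at best equal it. The women of most interest, positive on the MTT and negative on the OGTT, enter only as errors.

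The Introduction makes the choice more awkward. It describes the OGTT as unsuited to picking up mild early hyperglycaemia and as variable within the same woman, yet the sizing step seems to treat its result as the truth. At stake is whether 130, or the smaller number expected after the interim, can be cited as support for the comparative claim.

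**Working it through.** **1. Inputs.** From section 2.5: sensitivity 0.74, lower limit 0.62, N = 130, dropout 20%, hence 130 × 0.80 = 104 evaluable women. GDM prevalence is given as 3–5% for all pregnant women in the Netherlands and is expected to be higher here, without a figure. Cohort prevalence p is therefore an assumption, shown from 5% to 30%.

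**2. The plan's own figure.** A two-sided 95% Wald interval with lower limit 0.62 needs

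n = 1.96² × 0.74 × 0.26 / (0.74 − 0.62)² = 51.3, so 52 cases.

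With 20% dropout, 52 / 0.80 = 65. The stated 130 follows exactly if half the women are assumed to be cases: 52 / 0.5 = 104 and 104 / 0.80 = 130. The article does not state that prevalence. One-sample tests of 0.74 against 0.62 and exact limits with assurance were also tried; the nearest results after dropout were 119, 124, 152 and 153. In none of these routes does a difference between MTT and OGTT, or a complication rate, enter the calculation.

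**3. Which reference applies at the interim.** The trigger is completion of the OGTT in 25 women, at weeks 24–28 and before birth outcomes. The text says GDM is confirmed from glucose, and section 2.4 gives the only definition of GDM. OGTT-defined GDM is thus the only reference the text connects to this step.

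**4. What that reference implies.** Against OGTT-defined GDM, the OGTT has sensitivity 1 and specificity 1 by construction. The MTT's sensitivity (Se) is a fraction of the OGTT positives, so Se(MTT) − Se(OGTT) ≤ 0 whatever the data. With perfect specificity and sensitivity 0.74, the MTT finds 26% fewer women than the OGTT.

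With Sp for specificity, the MTT flags more women in total only if false positives outnumber false negatives:

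(1 − Sp)(1 − p) > (1 − Se) p, that is, 1 − Sp > 0.26 × p / (1 − p).

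| Assumed p | 0.26 p/(1 − p) | Specificity must be below |
|---|---|---|
| 5% | 0.0137 | 0.986 |
| 10% | 0.0289 | 0.971 |
| 20% | 0.0650 | 0.935 |
| 30% | 0.1114 | 0.889 |

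**5. Illustration (assumed p = 20%, 104 women).** OGTT positive: 20.8. MTT true positives: 0.74 × 20.8 = 15.4. Suppose the MTT flags 20 further women:

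- MTT positives rise to 35.4.
- Sensitivity stays at 0.74.
- Specificity falls from 1.00 to 1 − 20 / 83.2 = 0.76.

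The result is the same whether those 20 women later have complications or not. The calculation cannot tell a useful extra detection from a false alarm.

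**The case against.** A reader might infer that the whole study is locked into an OGTT reference and can neither support nor refute its hypothesis. The documents do not go that far.

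- Sensitivity and specificity are named only for sizing and re-sizing. Section 2.8 lists ANOVA, categorical tests, adjusted associations and mixed models, with no diagnostic-accuracy analysis, and defers detail to analysis plans that are not shown.
- No sentence names the reference standard. Confirming GDM incidence could simply supply the prevalence for a sizing formula. The standard behind the 74% cannot be seen.
- The Discussion relates glucose and insulin to fetal growth and birth weight, which do not depend on the OGTT, and intends a within-woman comparison of the two tests.
- At the 25-woman interim, GDM is the endpoint available. Complications could not replace it there.
- The study calls itself exploratory and says any markers would need validation in new studies.

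All of this stands, and it limits the point to the hypothesis and the basis for N. It does not remove it. Sensitivity and specificity are the only quantities the article ties to testing the stated hypothesis and to fixing N. The association described in the Discussion is not a comparison of MTT with OGTT and is not linked to N. An analysis plan can add a better comparison, but it cannot make an N chosen for another question support this one.

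A further temptation is to say that the MTT could win simply by lowering its cut-off. The hypothesis indeed sets no limit on false positives, but the article states no MTT cut-off and names specificity beside sensitivity, so that remains hypothetical.

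**Conclusion.** The point holds as a mismatch between the stated hypothesis and the basis for the sample size. Neither 130 nor the re-estimation rule supports the claim that the early MTT identifies more at-risk mothers than the OGTT. What they can address is how well a test detects OGTT-defined GDM.

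The conclusion rests on reading OGTT-defined GDM as the reference at the interim, a strong inference but not a statement in the text. Given that reading, the limit on MTT sensitivity is structural and needs no data. The specificity thresholds (0.986 to 0.889) depend on the assumed prevalence and on the article's 0.74, which was taken from 50 g OGTTs and not from the MTT. No corrected N is offered, because complication rates and paired detection rates are not given.

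The matter is best settled before the second interim, because that step may reduce N on a measure that does not bear on the comparison.

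**What to change.** 1. **Restate what N supports.** In sections 2.5 and 2.6, say that the sensitivity-based N and the re-estimation concern early prediction of later OGTT-defined GDM only, name that reference, and state that they do not power the comparison of at-risk mothers identified. Correct the null label at the same time.
2. **Add an exploratory end-of-study comparison.** Compare the early MTT with the 24–28 week OGTT in the same women, against the complications in section 2.7.5 and the birth-weight and fetal-growth outcomes in the Discussion. Examples are a paired difference in AUROC, or paired sensitivity with the MTT set at the OGTT's false-positive rate. Apply optimism correction to any cut-off derived from these data.
3. **Leave the interim where it is.** The outcome-based comparison cannot be made when 25 women have just had their OGTT.

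The cost is revised wording and analysis-plan text, since both tests and all outcomes are already collected in the same women. There are two downsides. Intervals will be wide at this N. Also, if care after a GDM diagnosis changes outcomes (an assumption; the documents do not describe that care), the comparison may be biased against the OGTT. That should be examined in a sensitivity analysis or stated as a limitation.
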